### **NTrainerRT® Therapy/Intervention**

The interventions will be initiated simultaneously with tube (gavage) feeds as early as 30 weeks postmenstrual age. Before and during each training session the infant will be evaluated for the following criteria:

*Criteria for Initiation of each NTrainer System® Therapy:*

1. Not on continuous vasopressor medications
2. Feeding in previous 48 hours.
3. Not mechanically ventilated. If the infant is on CPAP or Nasal canula >2 liters per minute, then the FiO2 must be <40%.

*Criteria for Exiting an NTrainer System® Therapy:*

1. If during an intervention the baby experiences Apnea/Bradycardic/Desaturation events requiring nursing stimulation or intervention during the training--hold training for one training session.
2. If the trainings are required to be held for 3 consecutive sessions, hold training for 1 day (24hours).
3. If NTrainer System® interventions are held for 3 days (72hours) and if GA is <32 weeks when ready to restart therapy interventions, then complete another 10 days of therapy sessions.
4. If NTrainer System® interventions are held for 3 days (72hours) and if GA is ≥32 weeks when ready to restart therapy interventions, then complete the remaining NTrainer System® sessions for a total of 10 days of therapy sessions.
5. If NTrainer System® interventions are held for 3 days (72hours) and the infant is on full oral feeds when ready to restart therapy interventions then discontinue any remaining NTrainer System® therapy sessions.

The NTrainer System® patterned synthetic orocutaneous stimulation will be delivered through a NICU (green) Soothie® silicone pacifier. A Wee Soothie® (purple) may be used if the baby is under 32 weeks and demonstrating behavior indicating that the size of the NICU Soothie® is aversive to the baby.

Infants in the **experimental group** will receive the NTrainer System® patterned synthetic orocutaneous stimulation **three to four times daily** during the first 30 minutes of a tube (gavage) feeding session or 30 minutes before oral feeding for 10-days distributed over a two week period. A single NTrainer System® stimulation regimen consists of a series of epochs given by: 3 minutes NTrainer System® ON, 5.5 minutes NTrainer System® OFF, 3 minutes NTrainer System® ON, 5.5 minutes NTrainer System® OFF, and 3 minutes NTrainer System® ON.

Infants assigned to the **control group** will receive a sham stimulation program in which the infant will be offered the same type of NICU Soothie® pacifier coupled to the receiver tube and handpiece, but not to the NTrainer System®. Infants assigned to the **control group** will be offered the pacifier by gently placing the pacifier on the lips. The pacifier should not be forced into the mouth and should not be moved in any manner that would represent any form of patterned input such as moving the pacifier in and out, tapping on the lips or face or massaging the mouth or oral facial structure. The sham will be presented **three to four times daily** at the beginning of the first 30 minutes of a tube (gavage) feeding session or 30 minutes before oral feeding. For each session if the baby does not latch onto the pacifier when it is offered, the use of the sham pacifier for that session will be discontinued. However, the infant will remain cradled in a supportive inclined posture for the duration of session. The sham will be used for 10-days distributed over a two week period. All other preparatory, infant positioning and sampling conditions will be equal among groups. The healthcare team will continue to promote feeding and growth as the standard of care for babies in the control group.

## **Breast Feeding**

Non-nutritive breastfeeding and nutritive breastfeeding practice will not be altered or changed by the NTrainer System® interventions. The availability of the mother will be taken into consideration for the scheduling of NTrainer System® interventions and no study intervention will interfere with breastfeeding behavior.

## **Safety**

To help ensure the safety of the study participants, temperature, heart rate, oxygen saturation, and blood pressure will be recorded daily throughout the therapy regimen.

## **OUTCOME MEASURES**

### **Primary Outcome Measure (Primary Study Endpoint) - Time to reach 100% full oral feedings:**

Time (in days) from initiation of oral feedings to the first oral intake that results in 100% oral feeding (definition of 100% oral feeding: no gavage supplementation and taking at least 120 milliliters per kilogram per day for 48 consecutive hours of breast milk, fortified breast milk or preterm formula as ordered by the child's physician. Decisions regarding oral feeding advancement will be made using the oral feeding advancement protocol (Appendix B) developed based on the study done by Simpson et al (2002).

### **Secondary Outcome Measures**

1. Feeding parameters:
  - a. The time (days) from the initiation of the NTrainer System® training to the first successful and four successful oral feeds in 24 hours.
  - b. Rate of milk transfer (ml/minute) at the time of full oral feeds—no gavage feeding.
2. Development of NNS parameters assessed by the NeoSuckRT® program
  - a. STI – STI NNS Index
  - b. Bursts/Minute
  - c. Events/Burst
  - d. NNS Events/Minute
  - e. % NNN Events
  - f. Total Events/Minute
3. Growth velocity from the initiation of NTrainer System® training to discharge.
  - a. Weight Gain (grams per kilogram per day)
  - b. Head Growth (centimeters per week). Occipitofrontal circumference - place measuring tape around the front of the head, above the brow and the occipital area. The measuring tape should be above the ears.
4. Length of hospital stay (days).
5. Necrotizing enterocolitis, aspiration pneumonia, and death events.
6. Ability to breast feed prior to discharge based on LATCH score.

During the study, adverse events will be monitored to ensure that the rate of reported events does not exceed the expected rate. Also, concomitant medications, concurrent procedures, therapies and protocol deviations will be documented.

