### **Inclusion Criteria**

1. Gestational age 26-32 weeks at birth, as determined by Dubowitz/Ballad examination and/or obstetric ultrasound done at less than 15 weeks.
2. At least 28 weeks post menstrual age at the time of enrollment.

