### **Exclusion Criteria**

1. Chromosomal abnormalities, multiple congenital anomalies or any major congenital anomalies including craniofacial malformation, cyanotic congenital heart disease, gastroschisis, omphalocele, diaphragmatic hernia or other major gastrointestinal anomalies, major neurological anomaly.
2. Infants with history of surgical necrotizing enterocolitis (stage III).
3. Infants with vocal cord paralysis.
4. Infants with neonatal seizures.
5. Infants with meningitis at time of enrollment.
6. Infants who are nipping all feeds at the time of enrollment.

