### **Data Analysis**

The primary outcome of the study is the time to attain full oral feeds. All subjects will be followed until they attain full oral feeds. Wilcoxon Rank Sum test will be used to test for a difference between the two groups. A secondary, supportive analysis will be performed using the log-rank test, with the understanding that this test will likely be underpowered. As mentioned in the sample size section, in the event that the rate of censoring is higher than the 10% of evaluable subjects expected, the Wilcoxon Rank Sum test will not be considered appropriate and the log-rank test will be elevated to the primary analysis method.

The null hypothesis is that there will be no difference in the median times to full oral feeds in the experimental group versus the control group, this will be tested using a 0.05 two-sided significance level, with the following hypotheses:

$$H_0 : M_{NT} = M_C$$

$$H_a : M_{NT} \neq M_C$$

Where  $M_{NT}$  and  $M_c$  refer to the population medians in the NTrainer System® group and the control group, respectively.

The time to event will be measured as the number of days from the initiation of oral feedings to full oral feeding. Kaplan-Meier survival curves will be produced to illustrate the time of attainment of full oral feeds in the two groups. As a supportive analysis, a Cox proportional hazards regression model will be used to test for a difference in the time to attain full oral feeds between the two groups, while controlling for age group (26-27, 27-28, 29-30 and 31-32 weeks post menstrual age) and the presence of co morbid conditions that interrupt the feeding schedule.

Exploratory subgroup analyses of the primary outcome in each of the different gestational age groups (26-27, 27-28, 29-30 and 31-32 weeks post menstrual age) will be performed to evaluate for any difference in

the effect of the NTraining® at different gestational ages, and within groups having and not having co morbid conditions that interrupt the feeding schedule.

The secondary outcome variables of time from the initiation of the NTrainer System® training to first and fourth successful oral feeds will analyzed in the same manner as the primary outcome variable.

The rate of milk transfer at the time of full oral feeds will be compared between groups using an independent t-test. We will also compare the NNS parameters after the completion of NTrainer System® and at the time of full oral feeds using *t* tests.

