### CRITERIA FOR THE INITIATION OF ORAL FEEDS:

1. Infant will have received an enteral tube feeding volume of at least 120ml/kg/day for at least 24 hours prior to initiation of oral feeding.
2. Infants on high flow nasal canula (>2LPM) or CPAP must be in < 40% FiO2.

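### The two secondary feeding milestones can be reached before their clock starts, and infants already past them dilute the comparison

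*Protocol*

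**What the plan says.** Under Secondary Outcome Measures, item 1a of the Protocol is "The time (days) from the initiation of the NTrainer System® training to the first successful and four successful oral feeds in 24 hours". The Hypothesis section names both milestones in the secondary hypothesis. The Data Analysis section says that these times "will analyzed in the same manner as the primary outcome variable": a rank-sum test, with the log-rank test as support or as substitute if censoring is high.

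Four other places decide who can be past a milestone at time zero:

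- Exclusion Criteria, item 6, removes only "Infants who are nipping all feeds at the time of enrollment".
- Inclusion Criteria, item 2, sets a floor and no ceiling on age: "At least 28 weeks post menstrual age at the time of enrollment".
- Appendix B opens oral feeding on enteral volume ("Infant will have received an enteral tube feeding volume of at least 120ml/kg/day for at least 24 hours prior to initiation of oral feeding") and an oxygen condition. Neither refers to enrolment or to training.
- NTrainerRT Therapy/Intervention gives an earliest start: "The interventions will be initiated simultaneously with tube (gavage) feeds as early as 30 weeks postmenstrual age". It gives no latest start and does not require that oral feeding has not begun.

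**The concern.** A time-to-event outcome needs every infant to be free of the event when the clock starts. The primary outcome meets this by construction, because its clock starts at the first oral feeding. Item 1a moves the origin to the start of training, and nothing replaces that protection. An infant taking one feed a day by mouth is eligible and may already have had a first successful feed. One taking five or six of eight may also have had four successful feeds in 24 hours.

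These infants get times of zero or less. Treatment cannot alter the times, but they hold the best ranks in both arms, so they pull the two distributions together. At stake is the power to see an effect on two milestones that the trial names in its hypotheses. The primary outcome is not affected.

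**Working it through.** **The plan's own figure.** For the primary outcome, with a difference of 5 days, SD 12, two-sided 0.05 and 80% power, n = 2 × [12 × (1.960 + 0.842) / 5]² = 90.4 per group. Dividing by 0.864, the minimum relative efficiency of the rank-sum test, gives 104.7, so 105. The stated sample size reproduces and is not in question. The Protocol states no power for item 1a.

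**Inputs.** From the Protocol: 105 per arm, two-sided 0.05, rank-sum test. Assumed, because the Protocol gives no values for item 1a: gamma times with mean 14 and SD 9 days in controls and mean 10.5 and SD 6.75 with NTrainer (25% shorter), and a share p of infants in each arm already past the milestone.

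**Why power falls.** The rank-sum test rests on the probability that a randomly chosen NTrainer infant beats a randomly chosen control. A pair carries information on treatment only if both infants are event-free at time zero, which has probability (1 − p)². All other pairs balance out at one half. The departure from one half therefore shrinks by (1 − p)², while the variance of the statistic hardly changes. Power of 85% corresponds to a standardised effect of 1.960 + 1.036 = 2.996. At p = 0.10 this becomes 2.996 × 0.81 = 2.427, and power is Φ(2.427 − 1.960) = 68%.

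**Results.** Columns 2, 5 and 6 are simulated; column 4 is the formula.

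| Share past the milestone | Power, plan as written | (1 − p)² | Power by formula | Fix, all prior events before randomisation | Fix, half between randomisation and first session |
|---|---|---|---|---|---|
| 0% | about 85% | 1 | 85% | – | – |
| 5% | 77% | 0.9025 | 77% | 81–83% | 80% |
| 10% | 67% | 0.81 | 68% | 80–81% | 75% |
| 20% | 48% | 0.64 | 48% | 75–78% | 59–60% |
| 30% | 31% | 0.49 | 31% | 69–70% | 45–49% |

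**Sensitivity.** Borrowing the primary outcome's figures instead (23 against 18 days, SD 12, normal times, affected infants set to day 0), power is 82% with none affected, then 77%, 65%, 47% and 31%. The loss depends mainly on the share affected, not on the assumed distribution.

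**Type I error.** With no treatment effect and 5% to 30% affected in both arms, simulated rejection rates were 4.7% to 5.7%, so the nominal 5% level holds.

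**The case against.** The strongest reply is that the Protocol intends training to come first. It starts training alongside tube feeds from as early as 30 weeks postmenstrual age. The Background says suck and swallow are not coordinated until about 32 to 34 weeks, and the principal subjects are born before 31 weeks. On that view few infants are past a first successful feed when training begins, and fewer still past four in 24 hours. The Study Time line and the feeding flow diagram are figures not shown and might settle the order. This stands as a limit on size: the share is unknown and probably smaller for the four-feed milestone. It does not close the gap, because an early start is permitted rather than required, and tube feeding at training start does not exclude partial oral feeding.

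A second reply is that handling of prior events belongs in a statistical analysis plan. But the origin, the events and the eligibility rules are all fixed in the Protocol, and together they produce the unusable times.

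Four stronger readings are tempting and are not supported:

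- *That the result is biased or falsely significant.* Affected infants should be spread evenly by randomisation. A chance imbalance in their number is ordinary sampling error, which the test allows for.
- *That the log-rank test fails on every such time.* It uses only the order of times, so a zero can be ranked. A negative time has no meaning as a survival time, but the test is only supportive unless censoring exceeds 10%.
- *That sessions scheduled "during the first 30 minutes of a tube (gavage) feeding session or 30 minutes before oral feeding" prove oral feeding before time zero.* They show that oral feeding is expected during the course. Nor do the two assessments required before the intervention necessarily take several days.
- *That the clock should move to randomisation.* Entry is possible from 28 weeks and training from 30, so the wait can be long. With no affected infants at all, a wait spread over 0 to 14 days cuts power from about 85% to about 73–75%, because the waiting time adds noise.

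**Conclusion.** The point holds as a flaw in the definition of two secondary outcomes. The rules allow infants past the milestone at time zero to enter the analysis with times that treatment cannot change. The consequence is dilution and lost power: under the assumptions above, from about 85% to 67% if 10% are affected and to 48% if 20% are. The share affected, the mean of 14 days and the 25% effect are assumptions, so the figures are a range and not an estimate for this trial. Neither the primary outcome nor the sample size is touched. The change is worth making because it is cheap, but it concerns secondary outcomes only.

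**What to change.** In Secondary Outcome Measures and Data Analysis, state that each milestone is analysed only in infants who had not met it at randomisation. That status can be read from the feeding chart and is fixed before allocation, so the randomised comparison is preserved. Report infants who had already met it as a baseline count by arm.

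Keep the origin at the first study session, and word it as NTrainer or sham so that it is defined in both arms. Count an infant who meets the milestone between randomisation and that session as day 0.

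The same edit should use one definition of the second milestone, since the outcome list refers to four successful feeds in 24 hours and the analysis section to the fourth successful feed.

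The cost is one baseline item, a sentence in each of the two sections, and a smaller denominator for these outcomes. The gain depends on timing. It is nearly complete if prior events precede randomisation and partial if many fall in the wait before the first session, as the last two columns of the table show. No change to treatment or to the feeding rules is involved.

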## **STATISTICAL ANALYSIS**

### **Sample Size Calculation**

The principal study subjects are infants born between 26 and 30 weeks gestation. The sample size was calculated based on the alternative hypothesis that the preterm infants born before 31 weeks gestation in the experimental group will transition initiation of oral feeds to attaining full oral feeds 5 days earlier than

the control group. Data from Simpson et al, (2002) demonstrate that infants who underwent a standard protocol for early oral feeding advance transitioned to the full oral feeds at  $23 \pm 12$  (Mean  $\pm$  SD) days. All subjects will be followed until they attain full oral feeds. Therefore it is expected that the time to full oral feeds will be available for all or nearly all subjects (i.e. there will be little or no censoring of event times). Since the time to full oral feeds may be right skewed, the Wilcoxon Rank Sum test will be used as the primary analysis. We consider 5 days to be a clinically significant difference between the control and the experimental group. Thus, 105 infants in each group of a two-sided alpha of 0.05 yield 80% power ( $\beta=0.2$ ) to detect a 5 day difference in the time to reach full feeds.

The percent of subjects with censored times are those leaving the trial prior to attainment of full oral feeds. Censored data will be assessed in a fully blinded way when 75% of the target sample size has completed the protocol. If rate of censoring is higher than 10% at this time, the planned use of the Wilcoxon Rank sum test will no longer be considered appropriate, and a log-rank test will become the primary analysis. Since the log-rank test has lower power, the sample size will need to increase to 160 subjects per group to achieve 80% power to detect a 5-day difference in median time to full oral feeds.

The infants between 31 and 32 weeks of gestation may attain full oral feeds much sooner compared to the younger gestation; therefore the effect size may vary considerably in this group of preterm infants. We will include the 25 subjects per group born between 31 and 32 weeks gestation to obtain pilot data on their effect size in order to calculate the sample size for this group, but the primary analysis will not include these subjects.

### **Data Analysis**

The primary outcome of the study is the time to attain full oral feeds. All subjects will be followed until they attain full oral feeds. Wilcoxon Rank Sum test will be used to test for a difference between the two groups. A secondary, supportive analysis will be performed using the log-rank test, with the understanding that this test will likely be underpowered. As mentioned in the sample size section, in the event that the rate of censoring is higher than the 10% of evaluable subjects expected, the Wilcoxon Rank Sum test will not be considered appropriate and the log-rank test will be elevated to the primary analysis method.

The null hypothesis is that there will be no difference in the median times to full oral feeds in the experimental group versus the control group, this will be tested using a 0.05 two-sided significance level, with the following hypotheses:

$$H_0 : M_{NT} = M_C$$

$$H_a : M_{NT} \neq M_C$$

Where  $M_{NT}$  and  $M_c$  refer to the population medians in the NTrainer System® group and the control group, respectively.

The time to event will be measured as the number of days from the initiation of oral feedings to full oral feeding. Kaplan-Meier survival curves will be produced to illustrate the time of attainment of full oral feeds in the two groups. As a supportive analysis, a Cox proportional hazards regression model will be used to test for a difference in the time to attain full oral feeds between the two groups, while controlling for age group (26-27, 27-28, 29-30 and 31-32 weeks post menstrual age) and the presence of co morbid conditions that interrupt the feeding schedule.

Exploratory subgroup analyses of the primary outcome in each of the different gestational age groups (26-27, 27-28, 29-30 and 31-32 weeks post menstrual age) will be performed to evaluate for any difference in

the effect of the NTraining® at different gestational ages, and within groups having and not having co morbid conditions that interrupt the feeding schedule.

The secondary outcome variables of time from the initiation of the NTrainer System® training to first and fourth successful oral feeds will analyzed in the same manner as the primary outcome variable.

The rate of milk transfer at the time of full oral feeds will be compared between groups using an independent t-test. We will also compare the NNS parameters after the completion of NTrainer System® and at the time of full oral feeds using *t* tests.

Weight gain (gms/kg/day) and Head Growth (cm/wk) will compared using independent t-tests, provided the data are reasonably normal. If the rates are highly skewed, the Wilcoxon rank sum test will be used.

Binary neonatal morbidity variables such as necrotizing enterocolitis, pneumonia and death will be compared between the two groups using the Cochran Mantel Haenszel (CMH) test, controlling for age group.

The length of hospital stay will be compared between groups using the Wilcoxon rank sum test, since this variable is typically right skewed.

The ability to breast feed prior to discharge (based on LATCH score) is a binary variable, and as such will be analyzed using the Cochran Mantel Haenszel (CMH) test, controlling for age group.

The number of apnea/bradycardia/desaturation free days prior to discharge, and the number of apnea/bradycardia/desaturation with feeds per day after reaching full oral feeds will be summarized descriptively. Statistical analysis of these variables may not be warranted since the decision to discharge may be closely linked to these values, and regardless of treatment group once they reach a certain level the discharge may occur.

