### **Randomization**

A stratified blocked randomization technique will be used. The subjects will be randomized to the **Experimental Group** or the **Control Group** and stratified into three groups based on their GA:

- 26-28 and 6/7 weeks gestation,
- 29-30 and 6/7 weeks gestation,
- 31-32 and 6/7 weeks gestation. (Pilot Study – Discontinued Spring 2013)

A blocked randomization technique will be used to ensure approximately equal number of subjects are in each group. The randomization will be generated by SAS v. 9.1 statistical software program. Just prior to randomization, the inclusion and exclusion criteria will be reviewed for each candidate.

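### The primary Wilcoxon test and its log-rank fallback omit the gestational-age strata used in randomisation, so they are conservative and less powerful than stratified tests if those strata differ in feeding time

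*Protocol*

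**What the plan says.** Protocol, Randomization: "A stratified blocked randomization technique will be used". The strata in the primary population are "26-28 and 6/7 weeks gestation" and "29-30 and 6/7 weeks gestation". A third stratum, 31-32 6/7 weeks, is a pilot. Sample Size Calculation says of its infants, "but the primary analysis will not include these subjects".

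Protocol, Data Analysis, on the primary outcome: "Wilcoxon Rank Sum test will be used to test for a difference between the two groups". If censoring exceeds 10%, "the log-rank test will be elevated to the primary analysis method". Neither test is described as stratified. The times to the first and to four successful oral feeds follow the primary method. For a further secondary outcome, "The length of hospital stay will be compared between groups using the Wilcoxon rank sum test".

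Age group does appear elsewhere in Data Analysis:

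- in a supportive Cox model of the primary outcome, "while controlling for age group (26-27, 27-28, 29-30 and 31-32 weeks post menstrual age";
- in exploratory subgroup analyses on the same bands;
- in the Cochran-Mantel-Haenszel (CMH) tests for morbidity and for breastfeeding ability.

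**The concern.** Blocked randomisation within strata makes the arms nearly equal in stratum composition. Differences between strata then contribute almost nothing to the true sampling variation of the treatment comparison. A pooled rank test still includes them in its reference variance. If the strata are prognostic, that variance is too large, so the actual size falls below the nominal 5% and power is lost against a test that ranks within strata.

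The protocol states where it adjusts for age, so a primary test named without adjustment reads as unadjusted. The secondary binary outcomes are then compared within age groups, while the test that decides the trial is not. The Cox model does not fill the gap. It is only supportive, and its bands overlap (26-27 and 27-28), are labelled as post menstrual age, and do not match the randomisation strata.

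**Working it through.** **Inputs from the protocol.** Effect 5 days, SD 12, mean 23, two-sided alpha 0.05, 80% power, 105 per group, and 160 per group if the log-rank test becomes primary (Sample Size Calculation). Two strata in the primary population (Randomization).

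**Assumptions, because the protocol gives no figure.** D is the difference in mean feeding time between the two primary strata, varied from 0 to 15 days. The strata are split 50:50, with 35:65 as a check. Blocks are of 4. The 12 days is taken as the total SD and held fixed.

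**Step 1: the plan's own figure.** For two means, n = 2 × (1.96 + 0.842)² × 12² / 5² = 90.4 per group. Dividing by the lower bound of Wilcoxon efficiency, 0.864, gives 104.65, so 105. The stated sample size reproduces. At the normal-data efficiency of 0.955, 105 per group gives 83.9% power.

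**Step 2: approximation for normal data, equal strata.**

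- Share of variance between strata: R² = (D/2)² / 144.
- Within-stratum SD: SDw = sqrt(144 − (D/2)²).
- Size of pooled test = 2 × (1 − Φ(1.96 / sqrt(1 − R²))).
- SEw = SDw × sqrt(2 / (105 × 0.955)) = 0.1412 × SDw.
- Pooled power = Φ(5/SEw − 1.96 × 12/SDw). Stratified power = Φ(5/SEw − 1.96).

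For D = 10: R² = 25/144 = 0.174, SDw = sqrt(119) = 10.9 and SEw = 1.54. Pooled size = 2 × (1 − Φ(2.156)) = 3.1%. Pooled power = Φ(3.245 − 2.156) = 86%. Stratified power = Φ(3.245 − 1.96) = 90%.

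The same formulas give a pooled size of 4.5% at D = 5 and 2.4% at D = 12. Power, pooled against stratified, is 84% against 85% at D = 5 and 87% against 93% at D = 12.

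**Step 3: simulation.** Pooled Wilcoxon against van Elteren, 105 per group, whole-day times, normal data, 50:50 strata, 20,000 runs per cell:

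| D (days) | Size pooled | Size stratified | Power pooled | Power stratified |
|---|---|---|---|---|
| 0 | 5.1% | 5.0% | 83.8% | 83.6% |
| 3 | 4.7% | 4.9% | 83.8% | 84.0% |
| 5 | 4.7% | 5.1% | 84.3% | 85.2% |
| 8 | 3.8% | 4.9% | 84.6% | 87.5% |
| 10 | 3.1% | 5.0% | 85.3% | 89.5% |
| 12 | 2.2% | 4.9% | 85.9% | 92.1% |

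The Monte Carlo standard error is about 0.15 points for size (sqrt(0.05 × 0.95 / 20,000)) and 0.26 points for power near 84%. A 35:65 split gives a similar picture: at D = 10, size is 3.4% against 5.2% and power 84.9% against 88.8%. Right-skewed (gamma) data with equal strata show a slightly larger loss: at D = 10, size is 2.9% against 5.0% and power 89.3% against 94.7%. Over all Wilcoxon cells run, including D = 15, the lowest pooled power is 83.5%.

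**Step 4: log-rank fallback.** 160 per group, 12% censoring, gamma data, 5,000 runs per cell:

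| D (days) | Size pooled | Size stratified | Power pooled | Power stratified |
|---|---|---|---|---|
| 0 | 4.9% | 5.0% | 83.7% | 84.5% |
| 5 | 4.7% | 5.1% | 84.8% | 86.4% |
| 10 | 3.9% | 5.2% | 86.6% | 91.1% |

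No calculation was made for length of stay, for which the protocol gives no SD.

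**The case against.** The strongest reply is that the effect depends wholly on D, which the protocol does not quantify. At 0-3 days nothing material happens, and at 5 days the loss is about one point. A loss of 4 to 6 points needs strata 10 to 12 days apart, and 12 days is a full SD between adjacent gestational-age bands. This stands, so the point has to be conditional.

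A reader might infer that the protocol itself says older infants in the primary population reach full feeds sooner. It does not. The remark in Sample Size Calculation is hedged and concerns infants of 31-32 weeks, who are outside the primary analysis. The choice to stratify on gestational age suggests that it was thought relevant, but gives no size.

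A reader might also infer that the primary result would be invalid or the trial underpowered. Neither follows. The error is conservative, and pooled power exceeds 80% in every Wilcoxon cell and in every log-rank cell at 160 per group. Nor is age ignored altogether: the Cox model of the primary outcome adjusts for age group, though only as support. The log-rank part matters only if censoring exceeds 10%.

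The argument does not extend to adding centre as a stratum. It is that the analysis should follow the randomisation factors, and gestational age is the only one named.

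Lastly, a statistical analysis plan, not at hand, could specify stratified forms. That is possible, but the protocol names the tests itself and says elsewhere where it adjusts for age, so its wording should be corrected in any case.

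**Conclusion.** The mismatch is real: randomisation is stratified by gestational age, and the tests named for the primary outcome, the time-to-feed secondary outcomes and length of stay are not. The consequence is an avoidable loss of efficiency that arises only if feeding time differs between the two primary strata. It ranges from nothing at 0-3 days to about 6 points of power at 12 days, with the size of the test falling to about 2.2%. These figures rest on 12 days being the total SD, on equal strata and normal data, and on an assumed range for D. The loss is measured against a stratified test and not against the planned 80%. This is a change worth making because it is nearly free; it is not a threat to the validity of the trial.

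**What to change.** Before unblinding, amend Data Analysis and the matching sentences in Sample Size Calculation as follows:

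- Make the primary test the van Elteren (stratified Wilcoxon) test, with the two gestational-age randomisation strata, 26-28 6/7 and 29-30 6/7 weeks, as strata.
- Stratify the log-rank test by the same two strata, both as the supportive test and as the fallback primary test.
- State that the time-to-feed secondary outcomes and length of stay are analysed with the same strata.

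The cost is a few lines of wording. The targets of 105 and 160 per group can stay, and the strata are already recorded at randomisation. If gestational age turns out not to be prognostic between the two strata, almost nothing is lost: 83.6% power against 83.8% in the simulation.
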